### 2.5. Randomization, Allocation, and Blinding

Randomization and blinding are controlled from the drug production source. All the test drugs are designed with the same appearance, dose, and smell, and each drug package has a corresponding drug number. Every six drug numbers are formed into a group, randomly corresponding to six test drugs, which necessarily include two mimetic granules of YWF, two HGWD granules, and two DSD granules, so that the whole is in accordance with the ratio of 1:1:1. Each center must recruit subjects in units of six (at least six subjects), and each recruited subject will be randomly assigned a sequential number and a corresponding drug number. Although the sequential and drug numbers are public, the specific properties of the drug are unknown to anyone, including subjects, investigators, and third-party inspectors.

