#### 2.6.1. Placebo-Control Group

From the beginning of chemotherapy, subjects in this group will take the mimetic granules of YWF brewed by warm water after meal twice a day (once 1 bag, 1 hour after breakfast and dinner) for at least 3 months. The mimetic granules of YWF, which contain 2.5% HGWD granules, 2.5% DSD granules, bitter principle, food colouring, and starch, are designed with the same appearance and dosage and similar smell and taste to YWF granules.

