Danggui Sini decoction (DSD) granules			
Danggui	*Angelica sinensis*	*Angelicae sinensis*	12
Guizhi	Cassia twig	Ramulus Cinnamomi	9
Baishao	Radix Paeoniae alba	Paeoniae Radix Alba	9
Xixin	*Asarum*	Herba Asari Cum Radice	3
Tongcao	Tetrapanax papyrifer	Medulla Tetrapanacis Papyriferi	6
Zhigancao	Honey-fried licorice root	Radix Glycyrrhizae Preparata	5
Dazao	Jujube	Fructus Zizyphi Jujubae	9

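### A fixed block of six that centres must know, with a placebo described only as similar in smell and taste, would amplify any failure of masking

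*Protocol article*

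**What the plan says.** **Blocks.** Protocol article, section 2.5: "Every six drug numbers are formed into a group, randomly corresponding to six test drugs". Every such block holds two packages of each product, placebo included. It continues: "Each center must recruit subjects in units of six (at least six subjects"). On concealment it says: "Although the sequential and drug numbers are public, the specific properties of the drug are unknown to anyone", and it names subjects, investigators and third-party inspectors as included.

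**Matching.** Section 2.5 says of the whole set: "All the test drugs are designed with the same appearance, dose, and smell, and each drug package has a corresponding drug number". Taste is not mentioned there. Section 2.6.1 describes one placebo for both active arms, the mimetic granules, "which contain 2.5% HGWD granules, 2.5% DSD granules, bitter principle, food colouring, and starch", and says they "are designed with the same appearance and dosage and similar smell and taste to YWF granules".

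**Products.** Table 3 lists five ingredients for HGWD, including astragalus and ginger, and seven for DSD, including angelica, licorice and asarum ("Herba Asari Cum Radice"). Cassia twig, white peony and jujube are common to both.

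**Who enrols and who rates.** Section 2.2 gives each centre an investigator who both enrols and collects data. The subject scores CIPN20, the primary outcome (section 2.7.1). The doctor grades neuropathy by CTCAE, a secondary outcome (section 2.7.2).

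**The concern.** Two stated features combine. First, the claims about masking differ. Section 2.5 asserts sameness of smell; section 2.6.1 asserts only similarity of smell and taste. Identical taste is claimed nowhere, although the granules are dissolved in warm water and drunk twice a day. One placebo also has to resemble two formulas of different composition.

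Second, a centre told to enrol in sixes must know the block size, and anyone holding the protocol can read the content. If a product were recognised in one patient, that would carry information about the patients still to come in the block.

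At stake are the enrolment decisions of an investigator who could foresee an allocation, and the CTCAE grades of a doctor who could infer one.

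**Working it through.** **1. Inputs.** Block of six with two of each product (section 2.5); 360 subjects, 120 per group (section 2.4); 30 centres (section 2.2). The documents give no rate at which products are recognised, so only the two extremes can be computed: no recognition, and complete recognition of all earlier allocations in the block. The calculation assumes that a centre finishes one block before opening the next.

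**2. The plan's own allocation figures.** 360 / 6 = 60 complete blocks, and 60 × 2 = 120 per group, which agrees with the plan. The average centre enrols 360 / 30 = 12 subjects, i.e. two blocks.

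**3. No recognition.** Each guess among three products is right with probability 1/3, so 6 × 1/3 = 2.00 of 6. For active against placebo, always guessing active gives 6 × 4/6 = 4.00 of 6. Knowing the block adds nothing.

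**4. Complete recognition.** With r packages left and n_k of product k among them, the best guess is right with probability max(n_k) / r. Averaging over the possible contents of the remaining block:

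| Packages left | Three products told apart | Only active v placebo told apart |
|---|---|---|
| 6 | 2/6 = 1/3 | 4/6 = 2/3 |
| 5 | 2/5 | (1/3)(4/5) + (2/3)(3/5) = 2/3 |
| 4 | 2/4 = 1/2 | (6/15)(1/2) + (8/15)(3/4) + (1/15)(1) = 2/3 |
| 3 | (3/5)(2/3) + (2/5)(1/3) = 8/15 | (3/15)(2/3) + (9/15)(2/3) + (3/15)(1) = 11/15 |
| 2 | (1/5)(1) + (4/5)(1/2) = 3/5 | (1/15)(1) + (8/15)(1/2) + (6/15)(1) = 11/15 |
| 1 | 1 | 1 |
| **Sum** | **101/30 = 3.37** | **67/15 = 4.47** |

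From four packages left downwards, the weights in the last column are the chances that 2, 1 or 0 placebos remain, out of the 15 ways to place two placebos in six positions. In the middle column, three packages left are two of one product and one of another with chance 3/5, or one of each with chance 2/5. Two packages left are the same product with chance 1/5.

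The excess is 3.37 − 2.00 = 1.37 of 6 (56% v 33% correct) for three products, and 4.47 − 4.00 = 0.47 of 6 (74% v 67%) for active against placebo.

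**5. Allocations fully determined before enrolment.**
- Three products: the last is always known, and the last two are known when they are the same product, chance 3 × 1/15 = 1/5. Total 1 + 0.20 = 1.20 of 6.
- Active v placebo: the last is always known. The last two are alike with chance 1/15 + 6/15 = 7/15, the last three are all active with chance 3/15, and the last four with chance 1/15. Total 1 + 11/15 = 1.73 of 6.

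**6. Other block sizes, three products, size known.**
- Three: 1 of 3 determined (33%).
- Six: 1.20 of 6 (20%).
- Nine: 1 + 3 × 3/36 + 3 × 1/84 = 1.29 of 9 (14%).

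Blocks of three would therefore make matters worse.

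**The case against.** The strongest reply is that no failure of masking is shown. The placebo was deliberately built with a little of each formula, a bitter agent and colouring. Each subject takes one product and has no other to compare it with. Different ingredient lists do not prove that the finished granules can be told apart. This stands: the documents show that perfect masking is not assured, not that masking fails.

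A second reply is that a known block helps staff predict the next allocation but tells a subject nothing about their own sachet. This also stands. A reader might infer that the block exposes the self-rated CIPN20. It does not; a subject's rating could be affected only through the taste or smell of the product itself.

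A third reply is that the text tells centres to enrol in sixes but does not say they are briefed on the two-of-each content. That is correct as far as it goes. Still, the content stands in the same paragraph of the protocol, so investigators who hold it can know it.

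Finally, a reader might infer that the trial makes no check of blinding. The document does not support this as a finding. It is a condensed article, the full protocol is not shown, and section 2.10 leaves the analysis plan to be written later. A guess asked for early would in any case be mixed with any real effect on acute neuropathy, which section 1 says about 90% of patients experience.

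**Conclusion.** The point holds as a modest, cheaply removed weakness. A single fixed block size, necessarily known to centres through the recruiting rule, gives away predictability for little return. Sections 2.5 and 2.6.1 also disagree on smell.

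The predictability gain is at most 1.37 of 6 correct guesses for three products and 0.47 of 6 for active against placebo, with 1.20 and 1.73 of 6 allocations determined in advance. These limits assume that every earlier allocation in the block is recognised before the next patient is enrolled. They fall to zero excess under perfect masking. The 56% and 74% should not be read as expected rates, and no bias in the treatment effect can be estimated from them. The exposure concerns enrolment and the doctor's CTCAE grade; the block alone does not unblind the subject who scores the primary outcome.

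**What to change.** 1. Delete the requirement that centres enrol in sixes from section 2.5.
2. Generate the drug-number list in blocks of randomly varying size, for example 6 and 9, and avoid blocks of 3. Keep block size and content in a document that sites do not receive, and ship supplies in quantities that do not reveal where a block ends.
3. Make sections 2.5 and 2.6.1 agree on smell, and state what is claimed for taste, including between HGWD and DSD.

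**Cost.** A changed randomisation and packaging list, since allocation is set at drug production, and two edited sentences. Balance within a centre becomes slightly looser: a last block left incomplete could leave two arms differing by up to 2 (block of 6) or 3 (block of 9) at that centre, whereas complete sixes leave no difference. With about 12 subjects per centre on average this is a small price.

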### 2.6. Intervention

All subjects will receive FOLFOX4 or mFOLFOX6 or XELOX chemotherapy regimen, listed in Table 2, and YWF granules or placebo at the same time. In order to control the dosage of Chinese herbal medicine, the standard granules will be used as the intervention dosage form in this study, provided by Tianjin Hongri Kangrentang Pharmaceutical Co. LTD., China, listed in Table 3. Besides, any other drugs potentially affecting the results of the experiment will be forbidden in the whole trial process, such as ganglioside, calcium and magnesium mixture agent, glutathione, mecobalamine, and injections containing astragalus.

#### 2.6.1. Placebo-Control Group

From the beginning of chemotherapy, subjects in this group will take the mimetic granules of YWF brewed by warm water after meal twice a day (once 1 bag, 1 hour after breakfast and dinner) for at least 3 months. The mimetic granules of YWF, which contain 2.5% HGWD granules, 2.5% DSD granules, bitter principle, food colouring, and starch, are designed with the same appearance and dosage and similar smell and taste to YWF granules.

#### 2.6.2. Intervention Group I

From the beginning of chemotherapy, subjects in this group will take HGWD granules brewed by warm water after meal twice a day (once 1 bag, 1 hour after breakfast and dinner) for at least 3 months.

#### 2.6.3. Intervention Group II

From the beginning of chemotherapy, subjects in this group will take DSD granules brewed by warm water after meal twice a day (once 1 bag, 1 hour after breakfast and dinner) for at least 3 months.

### 2.7. Outcomes

In order to observe the dynamic change of OIPN severity and quality of life (QOL) to give evidence-based evaluations, this trial sets multiple measure time points.

#### 2.7.1. Primary Outcome

The degree of oxaliplatin-induced peripheral neuropathy will be evaluated according to the score of European Organization for Research and Treatment of Cancer Quality of Life Questionnaire-CIPN twenty-item scale (EORTC QLQ-CIPN20, 20–80 scores, with higher scores meaning a worse outcome), which is evaluated by the subject on 1 day before and 3 consecutive days after the first time of oxaliplatin administration. Subsequent assessments will be made every one time from cycle 2 to cycle 6, 1 month after the end of cycle 6, and then every 3 months up to 1 year.

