## 1. Introduction

Oxaliplatin is a prime drug in the first-line standard chemotherapy regimens of colorectal cancer, included in mFOLFOX6, FOLFOX4, XELOX, and so on. The main side effect is dose-dependent neurotoxicity, namely, oxaliplatin-induced peripheral neuropathy (OIPN), which is the primary cause of reduction and cessation of platinum-based chemotherapy. Acute OIPN usually will develop in hours of oxaliplatin infusion and peaks 3 days later. About 90% of patients will undergo acute OIPN symptoms, characterized by abnormal sensations and muscle spasm of perioral region, tongue, throat, jaw, and limbs, triggered by cold stimulation. These acute symptoms can alleviate in a week or so but will recur as the next chemotherapy cycle comes subsequently [1, 2]. Chronic OIPN will gradually develop and aggravate after approximately 3 months of repeated administration, usually with more than 540 mg/m^2^ cumulative dose of oxaliplatin. Clinical manifestations of chronic OIPN are bilateral symmetric paresthesia, dysesthesia and/or allodynia of limbs (“glove-sock” distribution), disorder of fine motor coordination, sensory ataxia, and autonomic nervous dysfunction, persisting as long as 6 months or even years after the termination of treatment [2–4].

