#### 2.3.3. Termination Criteria

Subject withdraws from informed consent.Disease progression of subject is confirmed by imageological examination or clinical assessment.Subject experienced adverse events that the investigator deemed necessary to terminate trial treatment.Subject experienced severe side effects that the investigator deemed necessary to terminate trial treatment.Subject who stops or discontinues their medication without authorization.Subject who is less compliant with trial regulations intentionally or unintentionally.Other circumstances that may be detrimental to subject.

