21	Yangzhou Hospital of Traditional Chinese Medicine	Yangzhou, Jiangsu Province	[name]
22	Zhejiang Provincial Hospital of Chinese Medicine	Hangzhou, Zhejiang Province	[name]
23	Hangzhou Hospital of Traditional Chinese Medicine	Hangzhou, Zhejiang Province	[name]
24	The First Affiliated Hospital of Guangxi University of Chinese Medicine	Nanning, Guangxi Province	[name]
25	Henan Cancer Hospital	Zhengzhou, Henan Province	[name]
26	Affiliated Hospital of Traditional Chinese Medicine of Southwest Medical University	Luzhou, Sichuan Province	[name]
27	Affiliated Hospital of Shanxi University of Traditional Chinese Medicine	Xianyang, Shanxi Province	[name]
28	Hunan Academy of Traditional Chinese Medicine Affiliated Hospital	Changsha, Hunan Province	[name]
29	Hebei General Hospital	Shijiazhuang, Hebei Province	[name]
30	The First Affiliated Hospital of Guizhou University of Chinese Medicine	Guiyang, Guizhou Province	[name]

*Note*. Each center was randomly assigned the center number, and the ranking had nothing to do with the center scale and the number of planned enrollment.

**Table 2 tab2:** Chemotherapy regimen.

Abbreviated name	Components	Dosage	Mode of administration	Treatment course
FOLFOX4	Oxaliplatin	85 mg/m^2^	Intravenous infusion for >2 hours on day 1	Every 2 weeks, at least 3 cycles
	Leucovorin	200 mg/m^2^	Intravenous infusion for >2 hours on days 1 and 2	
	5-Fluorouracil	400 mg/m^2^	Intravenous injection on days 1 and 2	
		600 mg/m^2^	Continuous intravenous infusion for 22 hours on days 1 and 2	

mFOLFOX6	Oxaliplatin	85 mg/m^2^	Intravenous infusion for >2 hours on day 1	Every 2 weeks, at least 3 cycles
	Leucovorin	400 mg/m^2^	Intravenous infusion for >2 hours on day 1	
	5-Fluorouracil	400 mg/m^2^	Intravenous injection on day 1	
		1200 mg/m^2^	Continuous intravenous infusion for 22 hours on days 1 and 2	

XELOX	Oxaliplatin	130 mg/m^2^	Intravenous infusion for >2 hours on day 1	Every 3 weeks, at least 4 cycles
	Capecitabine	1000 mg/m^2^	Oral administration twice a day on days 1–14	

**Table 3 tab3:** Standard formulation of YWF granules.

Huangqi Guizhi Wuwu decocion (HGWD) granules			
Pinyin name	English name	Latin name	Doses, g
Huangqi	*Astragalus membranaceus*	Astragali Radix Membranacei	18
Guizhi	Cassia twig	Ramulus Cinnamomi	9
Baishao	Radix Paeoniae Alba	Paeoniae Radix Alba	9
Shengjiang	Ginger	Rhizoma Zingiberis Recens	9
Dazao	Jujube	Fructus Zizyphi Jujubae	9

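### Later primary-outcome assessments are dated only from the end of cycle 6, so subjects who stop chemotherapy sooner have no dated follow-up for chronic neuropathy

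*Protocol article*

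**What the plan says.** **Primary outcome (2.7.1).** CIPN20 is self-rated on the day before and the three days after the first oxaliplatin dose. After that: "Subsequent assessments will be made every one time from cycle 2 to cycle 6, 1 month after the end of cycle 6". Quarterly visits complete the chain until one year. No other starting point is given for these visits.

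**Secondary outcomes (2.7.2).** CTCAE grade and QLQ-C30 are taken the day before oxaliplatin in cycles 1 to 6, then on the same chain after cycle 6. The other two outcomes allow for a shorter course. RECIST treats the cycle 6 assessment as conditional on that cycle taking place. The cycle count may be recorded after whichever chemotherapy was last, with a reason if it is below six.

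**Chemotherapy (Table 2).** FOLFOX4 and mFOLFOX6: "Every 2 weeks, at least 3 cycles". XELOX: "Every 3 weeks, at least 4 cycles". No maximum is given.

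**Inclusion (2.3.1).** Subjects should be suitable for oxaliplatin at 85 mg/m² per dose and at least 540 mg/m² cumulatively.

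**Termination (2.3.3).** The list includes "Subject experienced adverse events that the investigator deemed necessary to terminate trial treatment" and "Subject who is less compliant with trial regulations intentionally or unintentionally". It does not say what happens to outcome assessment afterwards.

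**Introduction.** Oxaliplatin neuropathy is described as the side effect "which is the primary cause of reduction and cessation of platinum-based chemotherapy". The chronic form is said to develop after about three months, usually above 540 mg/m², and to last six months or even years after treatment.

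**The concern.** The visits after cycle 6 are where persistent neuropathy would be measured. If their dates exist only for subjects who complete six cycles, having a later score depends on tolerating oxaliplatin, which by the protocol's own account depends largely on neuropathy. Missing later scores would then be related to the outcome. If the granules work, more placebo subjects would be affected. Visits that were never held cannot be recovered by any later analysis plan.

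A second problem affects subjects who go past cycle 6. A visit meant to show the state after treatment may be taken while oxaliplatin is still being given.

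**Working it through.** No figure of the plan is at issue. The sample size of 120 per group neither supports nor refutes the point. The check sets the schedule beside the chemotherapy provisions.

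**Inputs.** Oxaliplatin 85 mg/m² every 2 weeks (FOLFOX) or 130 mg/m² every 3 weeks (XELOX), with minimum cycles 3 and 4 (Table 2). Cumulative dose at least 540 mg/m² (2.3.1). CIPN20 scheduled four times in cycle 1 and once in each of cycles 2 to 6 (2.7.1), so 4 + 5 = 9 scores up to cycle 6.

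**Formulas.** Cumulative dose = dose × cycles. End of cycle *k* = *k* × cycle length, assuming no delays.

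**1. Subjects who do not reach cycle 6**

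| Course | Cumulative dose | Ends at week | Dated CIPN20 scores | Dated visits afterwards |
|---|---|---|---|---|
| FOLFOX, 3 cycles | 3 × 85 = 255 mg/m² | 3 × 2 = 6 | 4 + 2 = 6 of 9 | none |
| XELOX, 4 cycles | 4 × 130 = 520 mg/m² | 4 × 3 = 12 | 4 + 3 = 7 of 9 | none |
| XELOX, 5 cycles | 5 × 130 = 650 mg/m² | 5 × 3 = 15 | 4 + 4 = 8 of 9 | none |

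The last row is the clearest. At Table 2's dose, such a subject is past both three months and 540 mg/m², where the Introduction places chronic neuropathy, and has no dated follow-up score.

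**2. Subjects who go past cycle 6**

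- FOLFOX at cycle 6: 6 × 85 = 510 mg/m², below 540. 540/85 = 6.35, so 7 cycles are needed: 7 × 85 = 595 mg/m².
- Cycle 6 ends at 6 × 2 = 12 weeks, and the visit one month later is at about week 16.
- With 7 cycles (ending week 14), the visit comes about two weeks after the last cycle ends. With 8 (week 16), it falls at about the end of the last cycle. With 9 or more, it falls during treatment.

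**3. Minimum cycles against the inclusion dose.** Both Table 2 minima (255 and 520 mg/m²) fall short of the 540 mg/m² in 2.3.1. That section's 85 mg/m² per dose also differs from Table 2's 130 mg/m² for XELOX. These passages must be reconciled.

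**4. Fallback.** Of the outcomes in 2.7, only the cycle count has an alternative date for a short course. CIPN20, CTCAE grade and QLQ-C30 have none.

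**The case against.** **The full protocol may cover this.** Figure 2 is not shown, and a fuller protocol exists that may contain an early-termination visit. This tempers the point but does not remove it. The article states a schedule, and that schedule conflicts with its own provision for fewer than six cycles. The visible note to Figure 2 adds only the four assessments in cycle 1.

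**The inclusion criterion expects FOLFOX subjects to pass cycle 6.** It does, but it describes suitability at entry, not the dose delivered. On XELOX at 130 mg/m², five cycles exceed 540 mg/m² without a cycle 6.

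**Early stoppers are not unobserved.** This stands. They have the cycle 1 scores, one CIPN20 score in each later cycle given, and a CTCAE grade before each dose. Neuropathy reported by then is on record. The gap lies in later scores and in any onset after the last scored visit.

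**The Introduction speaks of reduction as well as cessation.** This also stands. A reduced dose does not prevent a subject from reaching cycle 6, and no rate of early stopping is given.

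**Termination.** A reader might infer that 2.3.3 ends scoring. The text does not support that. Its two toxicity items concern trial treatment, and the section is silent on assessment throughout.

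**Conclusion.** The point holds as a defect in the stated schedule. Later CIPN20, CTCAE and QLQ-C30 visits have no date for subjects with fewer than six cycles, and may fall on treatment for those with more. The first gap depends on the outcome, given the protocol's statement that neuropathy is the primary cause of stopping. If the granules prevent neuropathy, losses would be heavier on placebo, and a comparison of the available later scores would tend to understate the benefit.

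The documents do not allow a size to be given. Two stronger inferences are tempting and are not supported:

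- **A calculated loss of power.** One could remove a share of neuropathy cases from the assumed 40% and 20% incidences and recompute power. That deletes cases already scored before stopping, and the share has no source. Starting from numbers already reduced for the 20% shedding allowance would also stack one loss on another. Moreover, the primary outcome is a 20 to 80 score, not an incidence.
- **Bias from mixing regimens at cycle 6.** Cycle 6 means week 12 and 510 mg/m² on FOLFOX, but week 18 and 6 × 130 = 780 mg/m² on XELOX. Random 1:1:1 allocation in blocks of six balances regimens between groups in expectation, so the mix adds variance rather than bias.

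**What to change.** 1. In 2.7.1 and 2.7.2, date the post-treatment CIPN20, CTCAE and QLQ-C30 visits from the last oxaliplatin dose, at one month and then at three-month intervals to one year, whatever the number of cycles given. Keep the in-cycle assessments as they are.
2. In 2.3.3, state that termination ends trial treatment only and that outcome scoring continues unless the subject withdraws consent.
3. Reconcile Table 2's minimum cycles with the cumulative dose in 2.3.1, along with the per-dose figures for XELOX.

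The cost is an amendment to the visit wording and a few more questionnaires and CTCAE gradings from early stoppers. Subjects who continue past cycle 6 would have their later visits at later calendar dates. No extra patients are needed, and no fixed-week visits need be added for everyone.
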